**Methods:**

We will carry out a feasibility study for a RCT of THN distributed in emergency settings at four sites, clustered by Emergency Department (ED) and catchment area within its associated ambulance service. THN is a peer-administered intervention. At two intervention sites, emergency ambulance paramedics and ED clinical staff will distribute THN to adult patients who are at risk of opioid overdose. At two control sites, practice will carry on as usual. We will develop a method of identifying a population to include in an evaluation, comprising people at risk of fatal opioid overdose, who may potentially receive naloxone included in a THN kit.

We will gather anonymised outcomes up to 1 year following a 12-month ‘live’ trial period for patients at risk of death from opioid poisoning. We expect approximately 100 patients at risk of opioid overdose to be in contact with each service during the 1-year recruitment period. Our outcomes will include deaths, emergency admissions, intensive care admissions, and ED attendances. We will collect numbers of eligible patients attended by participating in emergency ambulance paramedics and attending ED, THN kits issued, and NHS resource usage. We will determine whether to progress to a fully powered trial based on pre-specified progression criteria: sign-up of sites (*n* = 4), staff trained (≥ 50%), eligible participants identified (≥ 50%), THN provided to eligible participants (≥ 50%), people at risk of death from opioid overdose identified for inclusion in follow-up (≥ 75% of overdose deaths), outcomes retrieved for high-risk individuals (≥ 75%), and adverse event rate (< 10% difference between study arms).

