### Population B: predicted to be at high risk of death from opioid overdose

We will identify for inclusion in outcome follow-up people at high risk of fatal opioid overdose who may be able to benefit from naloxone from a THN kit. Population B thus extends the target population for follow-up of outcomes beyond original recipients of THN kits. We will define a discriminant function and use this as a predictive tool, similar to a risk index, incorporating known and routinely recorded predictors of opioid-related events. We will use existing linked data on opioid deaths in Wales, including ED and in-patient data, to select predictors most closely associated with those who died from opioid poisoning, and then use these predictors in our discriminant function to identify participants in the study site areas to be included in the ‘high-risk population’ (population B) for outcome analyses. We previously carried out scoping of NHS Wales ED and hospital routine datasets and linked ONS mortality records with these datasets. We found that we were able to describe circumstances of death for opioid overdose decedents who had visited EDs prior to their death, as well as describe service usage over a prolonged observation period. Mortality data were of high quality, as were data items on times and dates of attendances, outcomes of attendances, and demographic characteristics of attendees. Diagnostic and treatment data were of lower quality. Routine data in England will be captured from existing routine datasets as well as the recently implemented ECDS (Emergency Care Data Set); we will assess the quality of the data obtained from this source as a part of the research.

As ambulance service records are not routinely included in nationally available datasets that can be linked anonymously, we will assess whether the inclusion of potential participants from routine ambulance service data, e.g. patient records including flags such as ‘naloxone administered’ or ‘drug overdose’ improves the performance of the predictive tool. If this is the case, these data will be included in the final dataset used to identify the population in whom outcomes will be compared between intervention and control sites.

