### Consent

We will not attempt to gain consent to participate in the trial prospectively, at the time of attendance for opioid-related emergency, because that setting contradicts the requirements of informed consent [27]. We will not gather consent retrospectively, as the population is likely to be very difficult to reach and low contact rates could invalidate research findings. We will, however, consent patients to receive the intervention. Patients will do this by signing a training sheet, giving their name and date of birth as part of this process. In this way, we will gather some demographic information about the trainees and have a written record confirming that participants were trained to use the THN kit effectively.

As the wider population for inclusion in follow-up (population B) will be identified through anonymised routine data sources, we will not have identifiable data with which to contact people for consent purposes. Rather, we will offer the option to dissent from the research at all sites via patient information leaflets supplied with THN kits and made available at ED waiting areas. We will also include this information on the Wales Centre for Primary and Emergency (including unscheduled) Care Research (PRIME) website www.primecentre.wales. We have gained ethical, research, and information governance permissions to allow this study to follow this approach, in which all information about processes and outcomes of care will be anonymised to the research team except for clinical members at each site. These clinical researchers will split identifiable from clinical and operational study data before sending files separately to the NHS Digital in England and NWIS in Wales for linkage to routinely held outcomes in ED, in-patient, and mortality datasets held centrally; this split-file approach in which identifiable and clinical data are separated preserves patient anonymity [25].

For the qualitative component, we will obtain written informed consent from all service users and health care professionals who participate in interviews and focus groups. Service user participants will be identified by members of the NHS care team and third-sector drug treatment services. Participants will also be eligible to receive a thank you gift card voucher for their time.

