### Progression criteria

We will decide whether or not to proceed to a fully powered RCT using the following assessment principles and progression criteria:
Green: indicates that we have either met a criterion (in which case no modifications to the relevant aspect of the study protocol may be needed) or we are within 10% of our stated progression targets (in which case we will review the reasons for this and consider appropriate modifications to study methods)Amber: indicates that we are within 20% of our stated progression target, in which case we will critically review reasons for this and assess whether major changes to study methods are likely to realise significant improvementsRed: indicates that we are more than 20% from our target, in which case we will not, in the absence of clear extenuating circumstances, consider progression to a full trial

All the percentage changes will be measured as relative.

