### Intervention feasibility

Sign up of four sites, including ≥ 50% eligible staff to complete training in delivering the intervention at each intervention siteIdentification of ≥ 50% of people who have presented to ED or ambulance service with opioid overdose or an opioid use related problemTHN kits offered to ≥ 50% eligible patients at intervention sitesSerious adverse event rate of no more than 10% difference between intervention and control sites during the live trial period and prior to the conclusion of data collection

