### Safety monitoring

We will regard data on service usage (emergency and ITU admissions, and emergency attendances) and death as surrogate markers of adverse behavioural change in relation to opioid misuse, such as taking larger doses at one time. In doing so, we assume that increased rates of service usage and death correlate with an increased volume of higher risk drug-taking behaviour. We will also monitor for instances of serious adverse events, including deaths following THN use by interrogating routine health service data and also requests for data made to services on behalf of coroners across intervention and control sites. We include control sites because we expect THN to be available from specialist drug services in control sites.

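### The between-arm safety criterion includes deaths that presuppose take-home naloxone (THN) use, so on a relative, per-population scale it can worsen with kit supply while total deaths fall

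*Protocol article*

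**What the plan says.** In the protocol article, the Intervention feasibility list under Progression criteria requires an SAE rate of "no more than 10% difference between intervention and control sites during the live trial period" and on to the end of data collection. The abstract gives the same item as "adverse event rate (< 10% difference between study arms". Neither place gives a numerator, a denominator or a direction. On scale, Progression criteria states: "All the percentage changes will be measured as relative".

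The Safety monitoring section describes two streams. The first treats all deaths, admissions and emergency attendances as surrogate markers of riskier drug use, without reference to THN. The second concerns SAEs: "We will also monitor for instances of serious adverse events, including deaths following THN use by interrogating routine health service data". The sources are routine data and "requests for data made to services on behalf of coroners across intervention and control sites". The section adds: "We include control sites because we expect THN to be available from specialist drug services in control sites".

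Under Intervention, kits are offered by trial staff at intervention sites, and control patients are not offered one. Participant recruitment says it cannot be known whether a given kit will be used on its recipient or on a peer.

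**The concern.** The one SAE the article names can occur only where naloxone from a kit has been used. The reason given for monitoring control sites points the same way, because events counted regardless of naloxone would need no such justification. The trial's purpose is to raise kit availability in one arm. An overdose death in which a kit was tried and failed belongs to this category. The same death with no kit present does not. The between-arm contrast in this component therefore partly measures how many kits are in circulation.

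What is at stake is the progression decision. A red grade means that a full trial will not be considered unless there are clear extenuating circumstances. A safety criterion that worsens as uptake improves could count against an intervention that is reducing deaths.

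**Working it through.** The article gives no derivation for the 10% limit, so there is no figure to reproduce. The check is whether the named component can move in the opposite direction to total deaths.

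**Notation.** For each arm, let D be the number of overdoses, c the share in which THN is used, f1 the fatality with THN and f0 the fatality without it.

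- Deaths following THN use = D × c × f1
- All overdose deaths = D × [c × f1 + (1 − c) × f0]

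The article gives none of these inputs, so all values below are assumptions.

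**Illustration.** D = 1000 per arm, f0 = 4%, f1 = 2%, c = 10% in control and 20% in intervention.

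| | Control | Intervention | Relative change |
|---|---|---|---|
| Deaths following THN use | 100 × 0.02 = 2 | 200 × 0.02 = 4 | +100% |
| Deaths without THN | 900 × 0.04 = 36 | 800 × 0.04 = 32 | |
| All overdose deaths | 38 | 36 | −5.3% |
| Deaths per THN use | 2/100 = 2% | 4/200 = 2% | 0% |

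In percentage points of overdoses, the difference in the first row is (4 − 2)/1000 = 0.2.

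**Range.** The expected follow-up population of at least 1520 across four sites gives 1520/2 = 760 per arm. The assumptions are 0.1 to 0.4 overdoses per person-year, f0 = 5% and f1 = 1% to 4%. With D and f1 equal in both arms, the ratio of deaths following THN use is c(intervention)/c(control):

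- 5% to 10%: ratio 2.0
- 5% to 15%: ratio 3.0
- 10% to 12%: ratio 1.2

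Over the whole grid, total deaths are 0.4% to 8.3% lower in the intervention arm. The largest absolute difference arises with 0.4 × 760 = 304 overdoses, f1 = 4%, and c of 5% versus 15%:

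- Following THN use: 304 × 0.05 × 0.04 = 0.608 versus 304 × 0.15 × 0.04 = 1.824, a difference of 1.216/760 = 0.16 percentage points.
- Total: 304 × 0.0495 = 15.05 versus 304 × 0.0485 = 14.74, a ratio of 0.98.

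**Dilution by other SAEs.** Suppose deaths following THN use make up a share s of the control SAE count, the other events are equal in both arms, and the ratio is R. The relative rise in the whole SAE rate is then s × (R − 1). It exceeds 10% when s > 0.10/(R − 1), that is, above 10% for R = 2, 5% for R = 3 and 50% for R = 1.2.

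**Grading.** The article does not spell out how the 10% and 20% bands attach to an upper limit. If they are taken relative to the limit, green ends at 10% × 1.1 = 11% and amber at 10% × 1.2 = 12%. A rise of 20% or 100% would then be red. A looser reading gives a milder grade for the smaller rise.

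**The case against.** The strongest reply is that the article leaves the SAE set open and the rate undefined. The named event is introduced as an inclusion, not as the whole definition, so a reader who infers that every SAE counted must follow THN use goes further than the text. If all deaths were also counted as SAEs, the artefact would be diluted or absent. The denominator and scale matter as well: per THN use the ratio is 1.0, and on percentage points differences of 0.16 to 0.2 come nowhere near 10. These replies limit the point without removing it. The article applies a relative scale to its progression percentages, gives no per-use denominator and describes no collection of the number of THN uses. Any component conditioned on exposure carries the bias in proportion to its share.

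A second reply is that nothing stops automatically. The grading asks for a review of reasons, red allows for extenuating circumstances, the Data Monitoring Committee sees comparative data, and all deaths are monitored separately. This stands. It would be wrong to infer that a fall in deaths would go unseen or that the criterion is a hard stop. The criterion itself, however, is written on the SAE rate and not on those markers.

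A reader might also infer that THN use is traced better at intervention sites, because trial kits leave a record there: "Patients will do this by signing a training sheet, giving their name and date of birth as part of this process". The documents do not establish this. The SAE sources are the same in both arms. The sheet identifies the person trained, who may not be the person dosed, and it is not listed as an SAE source. No collection on drug-service kits is described in either arm. The remark "Diagnostic and treatment data were of lower quality" comes from scoping of Welsh data and is not specific to an arm. Unequal tracing is a plausible further worry, not a finding.

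**Conclusion.** The point holds in a limited form. The named SAE component depends on naloxone exposure, and the trial raises that exposure in one arm only. As a count or per-population rate on the relative scale, it increases in proportion to kit use: by 20% to 200% under the assumed ranges, while total deaths fall by 0.4% to 8.3%. The criterion could therefore be graded amber or red for an intervention that is working. This rests on assumed overdose, fatality and THN-use rates, and on deaths following THN use forming a sufficient share of the SAE count. It does not hold per THN use or on a percentage-point scale, and the article states neither.

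**What to change.** Base the between-arm safety criterion on events defined and found identically in both arms regardless of THN use: all opioid-poisoning deaths and all deaths. Mortality is already the proposed primary outcome (Outcomes), and all actual opioid-poisoning deaths are already needed for the sensitivity calculation (Discriminant function). State the denominator, for example the high-risk follow-up population at each site.

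Word the limit as an excess in the intervention arm only. If it stays undirected, a mortality benefit of more than 10% would itself breach it.

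Report the comparison with its uncertainty, because counts will be small. At 38 versus 36 deaths, the Poisson standard error of the difference is √(38 + 36) = 8.6, whereas 10% of 38 is only 3.8. Variation between two sites per arm adds to this. Crossing the limit on the point estimate should therefore prompt review and not be read as evidence of harm on its own.

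Take deaths and other SAEs following THN use out of the between-arm rate. Report them descriptively by arm, with the source of the kit where known.

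The cost is mainly wording, provided the death counts can be obtained by site, which the article does not state and should be confirmed. The downside is that all-death counts are less specific to naloxone, and the descriptive series covers that gap.

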### Data analysis

#### Discriminant function

To develop the discriminant function to be used for defining our population for outcome comparison, we will partition the available routine (retrospective) linked dataset, using one part (training data) to determine inclusion thresholds and the other (testing data) to check the performance of the function. We will use the actual number of recorded opioid poisoning deaths during the trial period to validate the function. We will summarise performance by calculating sensitivity (the proportion of actual opioid poisoning deaths included in our defined high-risk population; denominator = all actual opioid poisoning deaths, a/a+c) and positive predictive value (the proportion of our defined the high-risk population who die of opioid poisoning in the following year; denominator = all defined high risk, a/a+b) as shown in Table 1.

**Table 1 Tab1:** Sensitivity and positive predictive value of a discriminant function

	Actual opioid death	No opioid death	
Predicted high risk	a	b	a+b
Not predicted high risk	c	d	c+d
	a+c	b+d	

We will report on whether our discriminant function can, via Fisher’s linear discriminant function, be usefully reduced to a single individual-level risk score, consider thresholds used in its definition, and evaluate its performance as a predictive tool using test datasets compiled specifically for this purpose.

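### The retrospective test part is not shielded from predictor selection, and a single split is a noisier check of a rare outcome than resampling

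*Protocol article*

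**What the plan says.** Two sections of the protocol article describe how the risk function is built.

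- The section on Population B gives the data source: "We will use existing linked data on opioid deaths in Wales, including ED and in-patient data". The purpose of these data is "to select predictors most closely associated with those who died from opioid poisoning, and then use these predictors in our discriminant function". Selection is therefore driven by the outcome and comes before the function. No training or testing part is mentioned.
- The Discriminant function section, under Data analysis, introduces the split: "we will partition the available routine (retrospective) linked dataset, using one part (training data) to determine inclusion thresholds". It assigns the parts as follows: "using one part (training data) to determine inclusion thresholds and the other (testing data) to check the performance of the function". The only task named for the training part is the threshold.

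The same section plans two further checks. One uses later deaths: "We will use the actual number of recorded opioid poisoning deaths during the trial period to validate the function". The other is to "evaluate its performance as a predictive tool using test datasets compiled specifically for this purpose"; the source of those datasets is not described.

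Performance is summarised by sensitivity (a/(a+c) in Table 1) and positive predictive value (a/(a+b)). Under Trial method feasibility, the progression target is that at least 75% of those who die of opioid poisoning in the following year are included.

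**The concern.** A held-out part is an honest test only if it played no role in any step that used the outcome. Choosing predictors because they go with death is such a step. Taken literally, the article protects the testing part from threshold setting but not from selection. Chance associations among the test deaths can then help to choose the predictors and are counted again as good performance.

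The split also has a cost in precision. Opioid death is rare, so a test on part of the deaths is noisier than one that uses each death in turn. A function developed on part of the deaths also tends to rank people less well.

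At stake are the retrospective sensitivity and positive predictive value, and choices that lean on them. The Population B section names one such choice: ambulance records enter the final dataset if they improve the tool's performance. It does not say on which data that improvement would be measured.

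**Working it through.** **The plan's own figure.** There is none to reproduce. The article gives no count of retrospective deaths, number of candidate predictors, split ratio or expected test performance. All sizes below rest on assumed inputs, shown as ranges.

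**Step 1. Bias from selecting on all the data.** Assumptions: 50 to 400 deaths; 10 non-deaths per death; 20, 50 or 100 binary candidates, each present in 15% of non-deaths; 8 real predictors with log odds ratio 0.8 (odds ratio e^0.8 = 2.2); the 10 most strongly associated kept; a 50:50 split; Fisher's linear discriminant fitted in the training part; threshold set at 75% sensitivity there; 300 replicates. True performance comes from a separate sample of 3,000 deaths and 6,000 non-deaths. Overstatement = mean test sensitivity − mean true sensitivity, in percentage points.

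| Deaths | Candidates | Test | True | Overstatement, selection on all data | Overstatement, selection in training part only |
|---|---|---|---|---|---|
| 50 | 20 | 61.5 | 57.6 | 3.9 | 1.2 |
| 50 | 50 | 63.3 | 55.5 | 7.8 | −0.2 |
| 50 | 100 | 62.4 | 50.9 | 11.5 | 0.0 |
| 100 | 20 | 67.4 | 66.2 | 1.2 | −0.1 |
| 100 | 50 | 68.8 | 65.0 | 3.8 | 0.3 |
| 100 | 100 | 68.0 | 63.1 | 4.9 | −0.1 |
| 200 | 20 | 71.7 | 71.2 | 0.5 | −0.2 |
| 200 | 50 | 71.9 | 70.8 | 1.1 | 0.1 |
| 200 | 100 | 72.2 | 69.7 | 2.5 | 0.7 |
| 400 | 20 | 74.3 | 73.6 | 0.7 | 0.4 |
| 400 | 50 | 73.8 | 72.4 | 1.4 | 0.8 |
| 400 | 100 | 74.1 | 73.5 | 0.6 | −0.3 |

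The Test and True columns are for selection on all data. Selecting inside the training part removes the bias to within simulation error.

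With 50 candidates that are pure noise, selection on all data gives a test AUC of 0.643, 0.602, 0.576 and 0.554 at 50, 100, 200 and 400 deaths. The true value is 0.50.

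A second set of simulations used 40 candidates, 8 real, 10 kept, a 50:50 split and the highest 19% flagged, with weak and strong effects. It gave 3 to 6 points at 100 deaths, 2 to 3 at 200 and about 1 at 400. The two sets together give 1 to 6 points at 100 deaths.

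Positive predictive value was not simulated. Its direction follows from Table 1: for a given b, an inflated a raises a/(a+b) as well as a/(a+c).

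**Step 2. Precision.** The exact 95% interval for x captured out of n deaths has lower limit Beta(0.025; x, n−x+1) and upper limit Beta(0.975; x+1, n−x).

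- All 100 deaths, x = 75: 65.3% to 83.1%.
- A test half of 50, x = 38: 61.8% to 86.9%.

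In the second set (strong effects), ten-fold cross-validation with selection inside each fold was nearly unbiased. Its error SD was 0.060 against 0.076 for the split at 100 deaths (1 − 0.060/0.076 = 21% smaller), and 0.026 against 0.036 at 400 (1 − 0.026/0.036 = 28% smaller).

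**Step 3. Gain from building on all deaths.** Compared with a half-sample fit with selection in the training part, true AUC rises by 0.027 to 0.042 at 50 deaths, 0.021 to 0.041 at 100, 0.010 to 0.021 at 200 and 0.003 to 0.006 at 400. In the second set, capture rises by 1 to 4 points.

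**Step 4. Why all steps must be repeated.** At 50 deaths, with selection in the training part only, a threshold set at 75% there truly captures 54.2%, 47.0% and 40.9% of deaths with 20, 50 and 100 candidates. Fitting and threshold setting thus add their own optimism in the data on which they are done, so resampling must repeat them along with selection.

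**The case against.** The strongest reply is that the article does not commit to the leak. The Discriminant function section presents the split as part of developing the function, so the Population B section may give only the purpose and the later section the procedure. The article also does not say outright that the Welsh data and the partitioned dataset are the same. It states that the model will be fully specified within the study, and it leaves planned analyses to a SAP that is not shown. The predictors are described as known ones, so the search may be narrower than assumed here. A training and testing split is a recognised method.

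Much of this stands, and several stronger readings that a reader might infer are not supported:

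- *Selection uses the whole dataset, and the parts are halves.* The first is inferred from silence, and no ratio is given.
- *Population B is built from only part of the deaths.* Only the thresholds are tied to the training part. A final refit on all deaths is neither stated nor excluded.
- *The test result is a gate, or an optimistic result moves the threshold.* No section sets such a gate, and thresholds come from the training part.
- *The 75% criterion is inflated.* It is judged on deaths in the following year. These fall outside the retrospective data, so this leak cannot bias it.

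The reply does not remove the narrower point. The article assigns a task to the training part, and that task does not include selection. It also chooses a single split where a more efficient method needs no further data. The purpose-built test datasets cannot be counted as a safeguard while their source and independence are not described.

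**Conclusion.** The point holds in limited form. On a literal reading, and if both sections describe the same data, the testing part is not protected from predictor selection, so its sensitivity and positive predictive value may be optimistic. The single split is also less precise than resampling.

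The size depends on inputs that the article does not give. It is material at 50 to 100 deaths with many candidates and negligible at about 400. The harm is confined to the retrospective performance check and to the choice and quality of the function. The planned validation on trial-period deaths remains sound with respect to this leak. The change should be made because it is cheap and improves both bias and precision; the progression decision is not in doubt on this ground.

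**What to change.** Preferred: develop the final function on all retrospective deaths. Estimate sensitivity and positive predictive value by cross-validation or bootstrap that repeats predictor selection, fitting and threshold setting in every resample.

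If the split is kept: state that selection, fitting and thresholds are all done in the training part, and say whether the final function is then refitted on all deaths.

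In either case, keep the trial-period deaths as the independent validation, and report the number of deaths and of candidate predictors so that a reader can judge the likely optimism.

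The cost is a few sentences in the analysis section and some computing time, with no new data. The internal figure may come out slightly less favourable.
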